#### Post trial care

After the completion of the study protocol, all the enrolled subjects will further receive conventional rehabilitation services.

### Outcome measures

#### Primary measures

##### Fugl-Meyer assessment

Considering the motor paresis as one of the major manifestation of stroke and intense desire of stroke survivors to regain motor ability, the Fugl-Meyer assessment [11] (FMA) has been selected as a primary measure for the present study. FMA, a performance-based motor measure has five sections to examine motor, balance, sensation, range of motion and pain. The upper extremity motor section of FMA (FMA-UE) will be utilized in the investigation as a primary measure. The items of FMA-UE are hierarchically organized to quantify motor control in terms of reflexive, synergistic, mixed-synergistic, beyond-synergistic, coordinated movements. Specifically, FMA-UE is divided into 4 categories: upper extremity (18 items), wrist (5 items), hand (7 items), and coordination / speed (3 items). All items of each category are scored on a 3-point ordinal scale; ranging from 0 (no performance) to 2 (complete performance). FMA-UE is scored out of 66, with sub-score of 36 for the upper arm (FMA-UA) and 30 for the wrist and hand (FMA-WH). The mean FMA-UE scores (including FMA-UA and FMA-WH) at baseline, after 8-week intervention and 4-week follow-up will be considered for the analysis. FMA is a reliable and valid measure as well as most preferred for the poststroke motor related studies.

##### Nottingham sensory assessment (Erasmus MC modification of the revised version)

In view of the other primary objective, the somatosensory impairment will be assessed by the Erasmus MC modification of the revised Nottingham Sensory Assessment (Em-NSA). The measure comprises 5 somatosensory deficits to be assessed in the upper limb, namely light touch, pressure, pinprick, sharp-blunt discrimination, and proprioception. The deficits will be assessed as per the standard guidelines provided by the developers [12]. Each deficit is measured for the upper arm, forearm, hand and fingers, with a score range from 0 (absent) to 2 (no impairment) for every body part. The subtotal for each modality will be 8 with a total score for the Em-NSA as 40. The Em-NSA has demonstarted good to excellent intrarater and interrater reliability and validity and is a recommended and commonly used measure of sensory deficit in major neurological diseases including stroke [12].

Stereognosis will be assessed by the original NSA that comprises identification of 11 daily used items touch and manipulation in absence of vision. The assistance of the assessors in form of item manipulation will be imparted whenever required. Each item is score on 2-point rating (0 = absent to 2 = normal). The total stereognosis score range from 0 to 22. A score of 19/22 indicates impaired stereognosis. The stereognosis section of the NSA exhibited a moderate to good test-retest reliability among stroke subjects [1, 16]. Similar to the FMA, the analysis will be conducted for mean scores of total Em-NSA (including each sensory modality) and NSA (stereognosis) at postintervention and follow-up.

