#### Sample size

The power calculation has been conducted using the values for motor and sensory assessment from the two different studies [9, 10]. Considering the beta = 0.1 and α = 0.05, the calculation inferred that 53 subjects in each group would be sufficient to detect the desired change. However, to compensate possible drop outs (15%), 61 subjects in each group will be enrolled. Thus, the total sample size for the proposed investigation will be 122.

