#### Allocation

The subjects will be randomly allocated between the experimental and control groups in a block of 10. The randomization process will be conducted by an office staff, not associated with the study, using the SPSS Version 23 software. The intervention will be allocated in the ratio of 1:1. The assignment will be serially arranged in the coded digital files. The principal investigator ([name]) will enroll the potential participants and assign them into the respective group. The assessor will be unaware about the group allocation of the subjects.

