#### Statistical methods

The data will be analyzed by using IBM SPSS version 23.0. The demographic and baseline features of the study participants will be analyzed in form of mean (SD) / median (IQR) / n (%) and appropriate test [(Mann-Whitney U (U) / independent t (t) / chi-square (χ^2^)] tests will be used to analyze the difference for the characteristics between the groups. For inferential statistics, an intention-to-treat analysis method will be used by carrying forward the last observation for the missing data. A repeated-measures 2-way ANOVA (continuous data; within factor, time; between factor, group) will be used to estimate difference for the post intervention and follow-up scores between the groups. The pre-intervention score will be considered as the covariate with group as the independent variable and post-intervention or follow-up score as the dependent variable. The significance level will be set at *P* < .05.

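### Motor and sensory recovery are both primary, at two visits and one P < .05, with no lead visit and no rule on whether one or both must succeed, while the sample size covers a single test

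*Protocol article*

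**What the plan says.** All of the following is in the protocol article.

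- **Motor objective** (Outcome measures, Fugl-Meyer assessment): FMA-UE is introduced as a primary measure, not the only one. "The mean FMA-UE scores (including FMA-UA and FMA-WH) at baseline, after 8-week intervention and 4-week follow-up will be considered for the analysis".
- **Sensory objective** (Outcome measures, Nottingham sensory assessment): this section serves a second primary objective. "the analysis will be conducted for mean scores of total Em-NSA (including each sensory modality) and NSA (stereognosis) at postintervention and follow-up". The Em-NSA has five modalities. Stereognosis is scored separately on the original NSA.
- **Error level** (Statistical methods): "The significance level will be set at" P < .05. No split, order or adjustment is given. The section describes a repeated-measures ANOVA, and also a baseline-adjusted comparison with either the post-intervention or the follow-up score as outcome. It does not say which one decides.
- **Sample size**: the calculation was made "using the values for motor and sensory assessment from the two different studies". "Considering the beta = 0.1 and α = 0.05", it found that "53 subjects in each group would be sufficient to detect the desired change".

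The Perspective section expects sensory, motor and functional recovery all to improve, but it does not turn that into a criterion for success.

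**The concern.** Two objectives are primary and unranked, each is measured at two visits, and any result below .05 is significant. As written, the trial could be reported as positive on the motor total alone, the sensory total alone, stereognosis alone, or any of these at one visit only. The choice could be made after the results are known.

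The planned alpha of 0.05 and power of 90% describe one comparison. What they mean for the trial's claim depends on a success rule that is not stated. If one win is enough, the chance of a false positive claim exceeds 5%. If both are needed, the chance of success when the treatment works is below 90% unless one measure has power near 100%.

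**Working it through.** **Inputs from the Sample size section.** Alpha 0.05 (sidedness not stated; two-sided assumed), power 90%, 53 per group, 15% dropout, 61 per group enrolled. Allocation is 1:1 (Allocation section).

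**The plan's own figures.** The 53 cannot be reproduced, because no difference or SD is given. Solving backwards by the normal approximation, d = √(2/53) × (1.960 + 1.282) = 0.630 (0.636 by the t-test). The 61 is 53 × 1.15 = 60.95.

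**Scores and visits.** The narrow reading is two totals (FMA-UE, Em-NSA), or three scores with stereognosis, at 8 and 12 weeks. That is 2 × 2 = 4 or 3 × 2 = 6 comparisons. Counting subscores as well gives 3 motor + 7 sensory = 10 scores.

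**Rule A: any significant primary result counts.** With k independent tests the familywise error is 1 − 0.95^k:

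- k = 2: 9.75%
- k = 4: 18.5%
- k = 6: 26.5%

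Scores and visits are correlated, so these are upper values. The next table comes from simulating correlated normal test statistics. The correlations are assumptions; the protocol gives none.

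| Tests counted | Assumed correlation | Familywise error |
|---|---|---|
| Two totals, one visit | 0.9 down to 0 between scores | 7.0% to 9.8% |
| Two totals, two visits | 0.7 to 0.3 between scores, 0.9 to 0.7 between visits | about 12% to 16% |
| Two totals plus stereognosis, two visits | as above | about 15% to 22% |

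**Rule B: both totals must be significant.** Each test stays at .05 and the false claim rate does not exceed 5%. Assume each total has exactly 90% power, so each test statistic has mean 1.960 + 1.282 = 3.242. The chance that both pass is:

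| Correlation | 0 | 0.3 | 0.5 | 0.7 | 0.9 |
|---|---|---|---|---|---|
| Joint power | 81% | 82% | 83% | 85% | 87% |

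If the 53 is the larger of two requirements, the other measure has more than 90% power. With 99% on the other measure and independence, joint power is 0.90 × 0.99 = 89%.

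**Rule C: either total may succeed, with Holm across the two.** At 53 per group and d = 0.630:

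- Only one measure truly works: it must in general pass at 0.025, with power about 84%.
- Both work: power per measure is about 87-89% (correlation 0.9 to 0), because a win on one measure releases the full .05 for the other.

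**The case against.** **The subscores are only components.** FMA-UA, FMA-WH and the modality scores appear in parentheses, and the abstract lists just the two instruments. That is a fair reading, and the error ranges in the table do not count them. The point stands on the totals alone.

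**The alarming version.** A reader might count ten scores at two visits, 20 tests, and infer a 64% chance of a false positive (1 − 0.95^20). The documents do not support this. FMA-UE is the sum of its two parts (36 + 30 = 66) and the Em-NSA total is the sum of five modalities (5 × 8 = 40), so independence is impossible. Nor does the protocol say that a modality score may carry a claim by itself.

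**Error and power do not fail together.** A reader might also infer that the 5% and the 90% are both lost at once. They are not. If both measures are required, error is controlled. If either is enough, the chance of at least one win is above 90% (93-99% when each measure has 90%). Each rule damages one of the two figures.

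**The power figures are not the sponsor's.** This is correct. They rest on an effect solved backwards from 53, on equal power for both measures and on an unadjusted comparison; the planned baseline covariate could raise power.

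**A success rule may sit in an analysis plan.** Testing details often do, and none is shown here. But the article itself fixes the two primary objectives, the scores, the visits, the significance level and a sample size whose meaning depends on the rule. The objection is to what those statements do together.

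**Conclusion.** The point holds in this limited form. Two unranked primary measures at two visits, all tested at P < .05, leave the claim open to choice after the data are seen, and one alpha and one beta cannot describe it.

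If any primary result suffices, the familywise error is about 7-10% (two totals, one visit), 12-16% (two visits) or 15-22% (with stereognosis), and higher if subscores count. These ranges rest on assumed correlations. If both are required, error is controlled and power is 81-87% when each measure has exactly 90%. It comes close to 90% only if one measure has power near 100%. The protocol gives no effect size or SD with which to settle this.

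**What to change.** Before unblinded analysis:

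1. Name one score and one visit for each primary objective, for example FMA-UE total and Em-NSA total, both at 8 weeks. The choice of score and visit is the sponsor's; what matters is that it is fixed.
2. Make the subscores, the other visit and any score not named secondary.
3. State the success rule, one of two:
   - **Both required:** each at P < .05. Restate joint power from the motor and sensory inputs already used for the sample size; it is about 81-87% if each measure is at 90%.
   - **Either allowed:** Holm across the two. Restate power as about 84% for a measure that alone works, and about 87-89% per measure if both work, or recompute from the actual inputs.
4. Show the differences and SDs behind the 53 per group, so that the restated power can be checked.

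The cost is changed wording in the outcome, sample size and statistical sections, a less favourable stated power, and fewer results that can be claimed as primary. No extra patients or data are needed.

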#### Secondary measures

##### Semmes weinstein monofilament

Semmes-Weinstein monofilaments (SWM), standardized nylon fibres measure diminished cutaneous threshold. SWM filaments are graded to measure normal light touch, diminished light touch, diminished protective sensation, and loss of protective sensation. The filaments will be applied on palm (thenar and hypothenar areas) and fingers (tips and phalanges) of the upper limb to score the perceived response for the most sensitive to filaments. The cutaneous threshold is indicated in form of force ranging from 0.0045 (normal light touch) to 447 g (loss of protective sensation). SWM is considered to be a standard measure of assessing cutaneous threshold [17]. Further, it has been used in various stroke studies to measure the sensory deficits [15].

##### Two-point discrimination test

The two-point discrimination (2PD) test will be used to examine discriminative acuity, subject’s ability to perceive the two points being touched simultaneously. The static 2PD test using standard aethesiometer will be carried out in the palm and fingers of both the hands. The scoring will be noted in mm for the least distance between the perceived two points. The lesser the score the more will be the tactile acuity. In the proposed study, 2-PD measurement will be performed for the thenar and hypothenar areas (palm) and tips and phalanges (fingers). 2-PD is considered to be a reliable measure for stroke subjects [18].

##### Modified Rankin scale

The modified Rankin scale (mRS) [19], a universally used measure of disability will be utilized to evaluate the disability outcome of the NEPSER intervention in comparison to the standard rehabilitation regime. mRS scoring will be performed on ordinal scale range from 0 (no symptoms at all) to 5 (severe disability). mRS, a reliable and valid measure preferred to be an end point measure for stroke-related trials of new interventions.

#### Statistical methods

The data will be analyzed by using IBM SPSS version 23.0. The demographic and baseline features of the study participants will be analyzed in form of mean (SD) / median (IQR) / n (%) and appropriate test [(Mann-Whitney U (U) / independent t (t) / chi-square (χ^2^)] tests will be used to analyze the difference for the characteristics between the groups. For inferential statistics, an intention-to-treat analysis method will be used by carrying forward the last observation for the missing data. A repeated-measures 2-way ANOVA (continuous data; within factor, time; between factor, group) will be used to estimate difference for the post intervention and follow-up scores between the groups. The pre-intervention score will be considered as the covariate with group as the independent variable and post-intervention or follow-up score as the dependent variable. The significance level will be set at *P* < .05.

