**Fig. 1 Fig1:**
[figure not shown]
Timeline for schedule of enrolment, interventions, and assessment as per SPIRIT guidelines. -t1 = prior to enrolment, t1 = baseline assessment, t2 = assessment after 8 weeks of intervention, t3 = assessment after four-week follow-up (12 weeks after start of intervention). FMA = Fugl-Meyer assessment, Em-NSA = Erasmus MC modification of the revised Nottingham Sensory Assessment, NSA = Nottingham Sensory Assessment, SWM = Semmes-Weinstein monofilaments, 2-PD = Two-point discrimination, mRS = modified Rankin scale. NEPSER = **NE**uroplasticity-**P**rinciples-based **SE**nsory-**R**ehabilitation

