### Eligibility criteria

The subjects will be recruited if they exhibit the following key criteria: 1) Age - 20 to 80 years, 2) Hemiparesis (right or left) (as assessed by Fugl-Meyer assessment [11] upper extremity subsection: 0 to 66), 3) First episode of unilateral stroke, 4) Ischemic or hemorrhagic stroke, 5) 1 to 12 months after the stroke onset, 6) Impaired or more sensory deficit of any of the sensory modalities (< 7/8) [1] as discerned by Nottingham Sensory Assessment (Erasmus MC modification of the revised version) [12], and 6) Able to comprehend instructions and perceive assessments. However, the participants will be excluded if they demonstrate any of the following: 1) Receptive communication or other language disorder (which could interfere with the assessment and treatment process), 2) Contractures and deformities of hand / finger, 3) Complex regional pain syndrome, 4) Severe cognitive or perceptual deficit (as evaluated by the National Institutes of Health Stroke Subscales [13] and clinical tests: copying and drawing, line-bisection, cancellation tasks, and functional performance), 5) Diabetic or any other neuropathy, 6) Skin disorder, and 7) Peripheral nerve injury of either of the upper limbs.

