The NEPSER protocol will be imparted in a sequence of 4 levels, ranging from neural activation to functional usage of different sensory modalities.
Level I: Neural Activation
Mirror therapy (illusion of the normal sensory perception using mirror-box therapy);Sensory imagery (imagery of the normal sensory perception)These techniques may enhance the neural activation of the sensory cortex. The activation will provide a reasonable base for active sensory training. The perception such as various texture, size, shape, and objects will be used.Level II: Active Sensory-Training
The active sensory training for modalities such as tactile awareness and localization, texture recognition, and stereognosis will be provided by prolong-duration, meaningful and bimanual sensory perception.Level III: Sensori-Motor therapy
Motor therapy will be provided using specific stimuli (textured, shape) during activities.Level IV: Sensory-Functional therapy
Prolong-duration functional therapy using various meaningful shapes, sizes and textured objects of daily use will be provided.

The detail of execution of the experimental intervention is provided in Table 1. The regime will be imparted for 40 sessions, each 2 h, 5 sessions / week across 2 months. The assessments will be carried out at baseline, 8-week post-intervention and 4-week follow-up. During the follow-up duration, the subject will receive standard rehabilitation program.

**Table 1 Tab1:** Experimental intervention as per the type of sensory impairment and motor recovery stage of the hand

Sensory Impairment	Level of therapy	Motor Recovery Stage			
		BRS-H 1 & 2	BRS-H 3	BRS-H 4	BRS-H 5 & 6
**Light touch**	**Level-I**	MT (unilateral) – cotton / wool /soft toy	MT (bimanual) – cotton / wool /soft toy	MT (bimanual) – grasp-release, lateral prehension-release using cotton / wool /soft toy	MT (bimanual) – grasp and release, prehensile activity using cotton / wool /soft toy
	**Level-II**	Bilateral and unilateral perception of cotton / wool / soft toy (therapist applied)	Bilateral and unilateral perception of cotton / wool / soft toy	Bilateral and unilateral perception of cotton / wool / soft toy by grasp-release, lateral prehension and release	Bilateral and unilateral perception of cotton / wool / soft toy by prehensile activity

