#### Control group intervention

The control group will be provided same duration of standard rehabilitation program. The intervention will comprise of mirror therapy (movement based), motor therapy for the upper limb (utilizing activities such as pegs, blocks, pyramids, ball, and simulated sanding), and constraint–induced movement therapy. All the maneuvers will primarily comprise of motor tasks.

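### Last observation carried forward scores every patient lost before week 8 as unchanged, which dilutes a real effect under equal dropout and biases it in either direction under unequal dropout

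*Protocol article*

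**What the plan says.** The Statistical methods section of the protocol article gives one rule for missing outcomes: "an intention-to-treat analysis method will be used by carrying forward the last observation for the missing data". It applies to the inferential analyses, and no other method or sensitivity analysis is named. Those analyses are a two-way repeated-measures ANOVA and a comparison of post-intervention or follow-up scores with the pre-intervention score as covariate.

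The visit schedule is short: "The assessments will be carried out at baseline, 8-week post-intervention and 4-week follow-up". The Fig. 1 legend confirms that the last of these is week 12, and that nothing is measured between baseline and week 8.

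Three other statements bear on the point:
- Eligibility criteria: patients enter "1 to 12 months after the stroke onset".
- Control group intervention: "The control group will be provided same duration of standard rehabilitation program".
- Sample size: "to compensate possible drop outs (15%), 61 subjects in each group will be enrolled". Dropout is not split by arm or by time.

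**The concern.** Carrying the last value forward is harmless only if patients would not have changed after they left. Here the last value before week 8 is always the baseline score, so anyone lost during the treatment period is recorded as having recovered nothing at either endpoint. That is an unlikely average outcome for patients 1 to 12 months after stroke who were receiving intensive rehabilitation in either arm. Patients lost between weeks 8 and 12 are assumed to hold their week 8 score, although whether gains persist is what the follow-up visit is meant to measure. In both cases the filled-in value enters the model as a real measurement, with no added uncertainty.

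The estimates on both primary measures are at stake. Calling the approach intention-to-treat settles who is analysed and in which arm. It does not make the imputed values right. Because the article states this method outright, it is not a detail left to a separate analysis plan.

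**Working it through.** **Inputs from the article.** 53 evaluable and 61 enrolled per arm; 15% dropout; "Considering the beta = 0.1 and α = 0.05"; visits at baseline, week 8 and week 12.

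**Inputs assumed, because the article gives none.** Fugl-Meyer upper-extremity (FMA-UE) gain SD 6; baseline SD 18; mean gains of 10 (NEPSER) and 6 (control) for a true difference of 4, or equal gains of 8 or 4 for no effect; timing of loss and its split by arm; dropout completely at random; two-sided test.

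**1. The plan's own figure.** 53 × 1.15 = 60.95, rounded up to 61 per arm, 122 in total. This reproduces the article. (Dividing by 0.85 gives 62.35, so 63; that is a separate, small matter.) The 53 cannot be rebuilt, but with 90% power and two-sided 0.05 it implies a standardised difference of (1.960 + 1.282) × √(2/53) = 0.63.

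**2. Patients affected.** 61 × 0.15 = 9.15, so about 9 per arm have zero change imputed if all losses precede week 8.

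**3. Expected estimate at week 8.** With gains gE and gC, and shares pE and pC lost before week 8:

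LOCF difference = (1 − pE) × gE − (1 − pC) × gC

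When pE = pC = p this is (1 − p) × (gE − gC). A true effect shrinks by the factor 1 − p, and a null effect stays null.

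**4. Noise.** The variance of the change score in an arm becomes (1 − p) × SD² + p(1 − p) × g². For 15% loss in each arm and gains of 10 and 6:
- NEPSER: 30.6 + 12.75 = 43.35. Control: 30.6 + 4.59 = 35.19.
- SE = √(78.54/61) = 1.13, and 3.4/1.13 = 3.0, which is power of about 85%. Simulation gives 84%.
- Observed data: SE = 6 × √(2/51.85) = 1.18, and 4/1.18 = 3.4, which is power of about 92%.

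**5. Scenarios.** Baseline-adjusted ANCOVA at week 8, 61 per arm, simulated rejection rate at two-sided 0.05.

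| Gains NEPSER/control | Lost before week 8, NEPSER/control | Expected LOCF difference | Rejection with LOCF |
|---|---|---|---|
| 10/6 | 15%/15% | 0.85 × 4 = 3.4 | 84% (observed data 92%) |
| 10/6 | 7.5%/7.5% (half of 15% early) | 0.925 × 4 = 3.7 | 91% (observed data 94%) |
| 10/6 | 20%/10% | 8.0 − 5.4 = 2.6 | 61% (observed data 92%) |
| 8/8 | 15%/15% | 0 | about 5% |
| 8/8 | 20%/10% | 6.4 − 7.2 = −0.8 | about 11%, mostly favouring control |
| 8/8 | 10%/20% | 7.2 − 6.4 = +0.8 | about 11–12% |
| 8/8 | 5%/10% (half of 10%/20% early) | 7.6 − 7.2 = +0.4 | about 6% |
| 4/4 | 10%/20% | 3.6 − 3.2 = +0.4 | about 7% |
| 8/8 | 5%/25% | 7.6 − 6.0 = +1.6 | about 29–30% |
| 8/8 | 2.5%/12.5% (half of 5%/25% early) | 7.8 − 7.0 = +0.8 | about 11–13% |
| 4/4 | 5%/25% | 3.8 − 3.0 = +0.8 | about 11–13% |

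With no true effect, analysing observed scores keeps the type I error near 5%.

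**6. Second scale.** This uses the implied 0.63 SD effect, change SD 1 and all loss early.
- Equal 15% loss gives 0.85 × 0.63 = 0.535. Power is 0.84, 0.81 or 0.65 when control patients recover 0.63, 1 or 2 SD, against 0.88 to 0.89 without LOCF.
- With no effect, 10%/20% gives type I error of 7–8% and 5%/25% gives 11–19% for recovery of 0.63 to 1 SD. At 2 SD the figures are 16% and 49%, so the ranges in step 5 are not upper bounds.
- Offsetting cases exist: 10%/20% with control recovery of 0.63 SD gives 0.9 × 1.26 − 0.8 × 0.63 = 0.63, which is no bias.

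**The case against.** The best defence is that the article gives a single 15% figure. If loss is equal in the two arms, LOCF is conservative: there is no bias and the type I error is nominal when there is no effect, and a real effect is diluted by at most 15% when the loss is early. That stands. It also stands that the size of the problem is assumed throughout. Putting all losses before week 8 is the worst case for timing, and 5%/25% is an extreme split for a plan expecting 15%.

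A reader might infer that LOCF is set to produce a false positive for NEPSER. The documents do not support this. Contact therapy has the same duration in both arms. The described burden that differs is NEPSER's home programme of 2–3 hours a day with a log book (guidelines under Experimental group intervention). If that drives dropout, more patients leave NEPSER and LOCF works against it. The spurious-benefit rows need excess loss in the control arm. That is possible in a trial described as blinding only the assessor, but nothing in the article predicts it.

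It can also be said that patients who leave may recover less than completers, so a missing-at-random analysis could err the other way. That is fair. It argues for a sensitivity analysis, but does not make zero change a sound primary assumption.

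**Conclusion.** The point holds as a flaw in a stated method. The zero-change imputation follows directly from the article's own rule and visit schedule and needs no assumption. The direction and size of the bias do need assumptions.
- **Equal dropout:** a real effect shrinks by up to 15%. Under the assumed gains, the power loss runs from about 3 points (91% against 94%) to 8 points (84% against 92%), depending on how much loss is early.
- **More loss in NEPSER:** benefit is understated, 2.6 instead of 4 at 20%/10%.
- **More loss in control:** benefit can be overstated or created. For assumed recovery of roughly 0.67 to 1.33 SD (gains of 4 to 8 with SD 6), type I error is about 6–12% at 10%/20% and about 11–30% at the extreme 5%/25%.
- **Equal dropout and no true effect:** no bias.

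A general claim of inflated type I error, or of bias in NEPSER's favour, would go further than the documents allow. The firm conclusion is that LOCF cannot be relied on to be either unbiased or conservative here.

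**What to change.** In Statistical methods, drop LOCF as the primary approach. Analyse patients by randomised arm with a baseline-adjusted, likelihood-based mixed model for repeated measures, using all observed week 8 and week 12 scores. This is valid under missing at random. Add a multiple-imputation sensitivity analysis with a delta shift or a reference-based assumption, to show how the result changes if those who left recovered less than those who stayed. The change should be fixed before any unblinded analysis.

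The scores needed are already scheduled, so no visit is added. The cost is slightly more analysis work, and a primary result that relies on missing at random, which the sensitivity analysis is there to test.

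### The main analysis is described inconsistently, so the model, the role of baseline, the deciding contrast and the visit are not fixed

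*Protocol article*

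**What the plan says.** Four places in the protocol article bear on the analysis.

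- **Statistical methods, ANOVA sentence:** "A repeated-measures 2-way ANOVA (continuous data; within factor, time; between factor, group) will be used to estimate difference". It goes on to name the post-intervention and follow-up scores as what is compared. The levels of time are not listed.
- **Statistical methods, next sentence:** "The pre-intervention score will be considered as the covariate with group as the independent variable and post-intervention or follow-up score as the dependent variable". No time factor appears, and the outcome is one visit *or* the other.
- **Abstract, Methods:** the repeated-measures ANOVA alone, with no covariate.
- **Outcome measures, Fugl-Meyer assessment:** mean scores "at baseline, after 8-week intervention and 4-week follow-up will be considered for the analysis". The Nottingham section, which says it follows the Fugl-Meyer approach, names only the post-intervention and follow-up scores.

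Statistical methods sets significance at P < .05. It does not say whether the group effect, the group-by-time interaction or a single-visit contrast decides. The Sample size section plans for 90% power: "Considering the beta = 0.1 and α = 0.05, the calculation inferred that 53 subjects in each group would be sufficient".

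**The concern.** Baseline is one of three analysed time points in the Fugl-Meyer section, a covariate in Statistical methods, and absent from the model in the Abstract. It cannot sensibly be both a level of the time factor and the covariate in one model. The conjunction *or* also leaves open which visit counts.

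The candidate tests ask different questions:

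- With baseline as a level of time, the group main effect averages in a visit at which randomised arms are expected to be equal.
- With only the two later visits, the group-by-time test asks whether the effect changes between weeks 8 and 12, not whether there is one.
- With two separate ANCOVAs, there are two chances of a positive result at the same threshold.

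If the choice is made after the data are seen, the nominal 5% level no longer describes the procedure, and one data set could support opposite conclusions.

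**Working it through.** **Inputs from the article.** 53 evaluable per arm, beta 0.1, α 0.05 (Sample size); visits at baseline, 8 and 12 weeks.

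**Assumptions.** The article prints no difference, SD or within-patient correlation. I assume a two-sided test, SD 1 at each visit, compound symmetry with correlation r = 0.5, 0.7 or 0.9, and no baseline difference between arms.

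**The plan's own figure.** The 53 cannot be reproduced without an effect size, so I solve for the effect it implies. By the normal approximation, d = √(2/53) × (1.960 + 1.282) = 0.630. By the t-test, d = 0.636, which I use below. Then (n/2)d² = 26.5 × 0.404 = 10.71.

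**Noncentrality (λ) for each candidate test, same effect d at both visits**

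- Three-level ANOVA, group: the mean of (0, d, d) is 2d/3 and the variance of a patient's mean is (1+2r)/3. λ = 10.71 × (4/9) ÷ ((1+2r)/3) = 7.14, 5.95, 5.10.
- Three-level ANOVA, group-by-time (2 df): λ = 10.71 × (2/3) ÷ (1−r) = 14.3, 23.8, 71.4.
- Two-level ANOVA, group, unadjusted: λ = 10.71 ÷ ((1+r)/2) = 14.3, 12.6, 11.3.
- Two-level model with baseline covariate, group: λ = 10.71 ÷ ((1+r)/2 − r²) = 21.4, 29.7, 76.5.
- Two-level, group-by-time: λ = 0, since the two effects are equal.
- ANCOVA at one visit: λ = 10.71 ÷ (1−r²) = 14.3, 21.0, 56.3.

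**Power from the noncentral F**

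| Test | r = 0.5 | r = 0.7 | r = 0.9 |
|---|---|---|---|
| Three-level, group | 75% | 68% | 61% |
| Three-level, group-by-time | 93% | 99% | >99% |
| Two-level, group, unadjusted | 96% | 94% | 91% |
| Two-level, group, baseline-adjusted | >99% | >99% | >99% |
| Two-level, group-by-time | 5% | 5% | 5% |
| ANCOVA, one visit | 96% | >99% | >99% |

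The 5% row is only α: under equal effects, the hypothesis that this test examines is true. It shows that the test does not address benefit; it is not a loss of power.

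**Effect present at week 8 and gone by week 12.** The three-level group test has 26%, 23% and 20% power. The baseline-adjusted two-level group test has 63%, 77% and 99%. ANCOVA has at least 96% at week 8 and 5% at week 12.

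**False positives under no effect.** With 4,000 simulated trials per correlation, at least one of the two ANCOVAs is significant at 0.05 in 9.9%, 9.8% and 9.4% of trials. As a check, the two adjusted estimates correlate at r/(1+r) = 0.33, 0.41 and 0.47; the bivariate normal then gives 9.5%, 9.3% and 9.1%. If the three-level group and interaction tests could also count, the simulated figure is about 15%.

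**The case against.** The strongest reply is that there is only one analysis here. The ANOVA sentence is aimed at the post-intervention and follow-up scores, and the sentence after it adds the baseline score as covariate. Together they can describe one repeated-measures ANCOVA on weeks 8 and 12. Its group test is a clean average effect with more than the planned power. The Fugl-Meyer wording need not contradict this, since a covariate is also considered for the analysis. A condensed article may also leave the deciding contrast to the full protocol or analysis plan.

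Much of that stands. A reader might infer that the article prescribes two irreconcilable primary analyses, or that no ANOVA test answers the question. The documents support neither. The text labels neither model primary, the two-level group test is sound, and the three-level interaction is a valid test of differential change, though it gives no effect at a named visit. A reader might also infer that the ANOVA is what forces last observation carried forward; the article ties that rule only to intention-to-treat.

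The reply does not remove the inconsistency. The single-model reading has to set aside the *or* in the covariate sentence and the covariate-free Abstract, and it has to take baseline in the Fugl-Meyer list as a covariate. It still leaves the contrast and visit unnamed. The point is not that detail is absent, but that the statements the article does make do not agree.

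**Conclusion.** The point holds as an ambiguity that should be removed, not as a proof that the planned analysis is invalid. Under the favourable reading the plan is sound and well powered. Under the reading with baseline as a level of time, the group main effect estimates two thirds of the treatment effect, with about 61–75% power against the planned 90%. If either of two single-visit ANCOVAs may count, the false-positive rate per outcome is roughly 9–10% instead of 5%.

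The power figures rest on an implied d of about 0.64, equal effects at both visits, compound symmetry and correlations of 0.5–0.9, none of which the article prints. That the tests answer different questions does not depend on those values.

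**What to change.** Replace both model sentences in Statistical methods with one mixed model for repeated measures:

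- **Outcomes:** the 8- and 12-week scores.
- **Fixed effects:** group, visit, group-by-visit, baseline score and baseline-by-visit.
- **Covariance:** unstructured within patient.
- **Baseline:** covariate only, never a level of time.
- **Primary contrast:** one, named in advance. For example, the adjusted group difference at 8 weeks (end of intervention) with its 95% CI, and the 12-week difference from the same model as secondary.

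Align the Abstract and the Fugl-Meyer section with this, and settle it before outcomes are looked at by arm. No further covariates are needed to resolve the ambiguity. With complete data, the 8-week contrast agrees with the single-visit ANCOVA already described, so the intent of the covariate sentence is kept.

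The cost is one paragraph and two small wording changes. No data are added, and the SPSS software already named can fit the model. The one real concession is that the investigators must choose a primary visit and accept the other as secondary.
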